#### 2.11.2 Statistical methods for analyzing efficacy outcomes

For primary and secondary efficacy endpoints, descriptive statistics will be presented by treatment group, and comparisons will be made both between groups.

For between-group comparisons, changes from baseline (post-8-weeks consumption minus pre-consumption) will be analyzed using independent *t*-test if normality assumptions are met, or Mann-Whitney U test if not. The proportion of participants showing improvement in efficacy variables at 8 weeks compared to baseline may be analyzed using Chi-Square test or Fisher’s exact test.

For repeated measurements of FSS (excluding the primary efficacy endpoint analysis), VAS for subjective fatigue, and grip strength (measured three times), RM-ANOVA or Linear Mixed Model will be used for between-group comparisons if normality assumptions are met or appropriate non-parametric methods if not. In cases of severe violation of normality assumptions, variable transformation methods such as logarithm transformation may be applied before analysis.

Additionally, ANCOVA or ranked ANCOVA may be performed with covariates including lifestyle factors (dietary intake, physical activity, alcohol consumption, smoking, occupation, etc.), baseline values and changes in lifestyle factors, baseline values of efficacy variables that are not homogeneous between groups, and demographic information.

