### 2.4 Outcomes

#### 2.4.1 Primary outcomes

The Fatigue Severity Scale (FSS) scores change from baseline to 8 weeks is designated as the first primary outcome (17, 18). The FSS is a self-administered questionnaire consisting of 9 items that evaluate the subjective level of fatigue-related disability on a scale of 1–7. Scores below 27 indicate “low fatigue,” scores between 27 and 44 indicate “medium fatigue,” and scores of 45 or above indicate “high fatigue.” FSS will be measured at baseline, 4 weeks, and 8 weeks.

The second primary outcome is the change in time and distance to exhaustion during a treadmill exercise test from baseline to 8 weeks. The exercise test utilizes the Modified Bruce protocol, which progressively increases both speed and incline to measure exercise capacity (19). The test begins at stage 1 (2.7 km/h, 0% grade, 3 min) and continues through predefined stages of increasing difficulty (stage 2: 2.7 km/h, 5% grade, 3 min; stage 3: 2.7 km/h, 10% grade, 3 min; stage 4: 4.0 km/h, 12% grade, 3 min; stage 5: 5.4 km/h, 14% grade, 3 min; stage 6: 6.7 km/h, 16% grade, 3 min; stage 7: 8.0 km/h, 18% grade, 3 min). The test is terminated when the participant voluntarily requests to stop. The distance to exhaustion is calculated using the total exercise duration and speed. Treadmill exercise test will be conducted at baseline, and 8 weeks.

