### 2.6 Sample size

The sample size of this clinical trial is 50 participants per group. Although no preliminary data on PKL extract’s anti-fatigue effects in humans are available, we referenced a study using fermented porcine placental (FPP) extract (26), which has received Korean MFDS approval for fatigue improvement, as PKL extract is pursuing the same regulatory pathway. In that study, the FPP group (*n* = 36) showed a mean change in FSS score of −9.79, while the placebo group (*n* = 31) demonstrated a mean change of −5.20. Based on the reference study data showing a mean difference of 4.59 points in FSS score change between treatment and placebo groups, and assuming a pooled standard deviation of 6.8, we calculated the required sample size. With a significance level of 0.05 and a power of 0.8 for a two-sided test, we estimated that a minimum of 35 participants per group would be required. Considering an anticipated dropout rate of approximately 30% during the clinical trial process, we decided to recruit a total of 100 participants, with 50 participants per group.

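### VAS and grip strength have two between-group analyses with no rule on which governs, and the repeated-measures comparison fixes neither the tested term nor the role of baseline

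*Protocol article*

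**What the plan says.** Section 2.11.2 opens by covering primary and secondary efficacy endpoints together and then sets the general rule: "For between-group comparisons, changes from baseline (post-8-weeks consumption minus pre-consumption) will be analyzed using independent" t-test, or by Mann-Whitney if normality fails. VAS and grip strength are secondary endpoints in section 2.4.2, so this rule covers them.

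The next paragraph of 2.11.2 takes the repeated values of FSS, VAS and grip strength, described as measured three times, and says that "RM-ANOVA or Linear Mixed Model will be used for between-group comparisons if normality assumptions are met", with non-parametric methods otherwise. The primary FSS analysis is excluded from this paragraph by name. VAS and grip have no matching exclusion. Covariate adjustment, including for baseline values that differ between groups, appears only as an additional analysis that may be done.

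On visits, section 2.4.1 states that "FSS will be measured at baseline, 4 weeks, and 8 weeks", and section 2.9 takes the FSS baseline from screening. The text shown gives no visit list for VAS or grip, and Figure 1 is not shown. Section 2.11.1 sets significance at p < 0.05.

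**The concern.** There are two separate problems.

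1. **Competing tests.** For VAS and grip, the change-score test and the repeated-measures comparison are both between-group analyses of the same outcome at the same level. They can disagree, and the plan does not say which one is the result. The authors resolved this overlap for FSS but not for the other two outcomes.

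2. **Open target of estimation.** A between-group comparison from RM-ANOVA or a mixed model can mean the group main effect, the group-by-time interaction (2 degrees of freedom for three visits) or a contrast at one visit. Baseline can be a response or a covariate. These answer different questions. If the pre-dose value is one of the averaged responses, the group main effect includes a visit at which randomisation makes the expected difference zero.

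At stake are the size and reliability of the supportive fatigue and strength results, and the freedom to choose among tests after seeing the data.

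**Working it through.** **The plan's own figure.** Section 2.6 gives these inputs: "With a significance level of 0.05 and a power of 0.8 for a two-sided test"; "a mean difference of 4.59 points in FSS score change between treatment and placebo groups"; "assuming a pooled standard deviation of 6.8". Then n = 2 × (1.960 + 0.842)² × 6.8² / 4.59² = 34.5, so 35 per group. This agrees with "a minimum of 35 participants per group would be required". Allowing for 30% dropout, 35 / 0.70 = 50. A t-based calculation gives 35.4, and power with 35 is 79.5%. The stated size reproduces. The document gives no figure for the repeated-measures analysis.

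**Dilution, if the group main effect over three visits is used.** It estimates (0 + d4 + d8)/3, where d4 and d8 are the true differences at weeks 4 and 8.

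| Week-4 effect | Share of d8 | Loss | 4.59 FSS points becomes |
|---|---|---|---|
| equal to d8 | 2/3 | 33% | 3.06 |
| half of d8 | 1/2 | 50% | 2.30 |
| none | 1/3 | 67% | 1.53 |

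The group-by-time term, a week-8 contrast from baseline, and a model with baseline as covariate use the pre-dose value as a reference and are not diluted.

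**Power.** Assumptions, none given by the plan: 35 per arm, SD 1 at each visit, equal correlation ρ between visits, and a true effect of 0.6 SD at both weeks 4 and 8. The variances per participant are:
- week-8 change: 2(1 − ρ)
- mean of three visits: (1 + 2ρ)/3
- week-8 value adjusted for baseline: 1 − ρ²

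The noncentrality is effect × √(35/2) / √variance. At ρ = 0.5:
- change test: 0.6 × 4.183 / 1.000 = 2.51
- group main effect: 0.4 × 4.183 / 0.816 = 2.05
- baseline-adjusted week 8: 0.6 × 4.183 / 0.866 = 2.90

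| ρ | Change test | Group main effect | Baseline-adjusted week 8 |
|---|---|---|---|
| 0.3 | 55% | 62% | about 73% |
| 0.5 | 70% | 52% | 82% |
| 0.7 | 89% | 45% | 93% |

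Group-by-time has 73% power at ρ = 0.5.

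The same comparison on the section 2.6 FSS figures, holding the SD of change at 6.8, gives for ρ = 0.3 / 0.5 / 0.7:
- group main effect: 85 / 62 / 36% if the effect is complete by week 4, and 62 / 40 / 23% if it builds linearly
- change test: 79.5% throughout
- baseline-adjusted week 8: 93 / 90 / 86%

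**False-positive chance per outcome, no true effect.** Simulated with 35 per arm and ρ from 0.3 to 0.7, the chance that at least one test reaches p < 0.05 is:
- change test plus interaction: about 7-8%
- change test plus group term: about 9.5-10%
- all three: about 12%

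**The case against.** The strongest reply is that the dilution is assumed. A reader might infer from three measurements and a between-group comparison that the plan averages baseline into the treatment effect. The document does not say so: it names no term and does not say whether baseline is a response. A group-by-time test, a week-8 contrast or a mixed model with baseline as covariate all fit the same sentence. This stands, so the loss of a third to two thirds is conditional.

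Lost power is not general either. At ρ = 0.3 with the full effect by week 4, the group main effect has more power than the change test (62% against 55%). Likewise, the 12% figure needs all three tests to be in play. If the interaction is the only repeated-measures term read, the figure is 7-8%.

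The visits for VAS and grip are inferred. Three visits fit the 4-week evaluation interval, but for grip the word three also matches the three efforts at each test in section 2.4.2. Those efforts are reduced to the highest value, so three visits remains the likelier reading, though it is not stated in the text shown.

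Finally, model terms and covariance structure are commonly left to an analysis plan, and one may exist. That answers the silence on the model term taken alone. It does not answer the overlap, which is in the text: two stated rules cover VAS and grip, and an analysis plan would have to override one of them to leave a single governing test.

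**Conclusion.** The point holds as an unresolved overlap plus an open choice of estimand. It is worth correcting, but it is not a defect of the primary analysis.

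- **Certain from the text:** two between-group analyses for VAS and grip with no order between them, and no stated term or handling of baseline for VAS, grip and by-visit FSS.
- **Conditional:** a 33% to 67% understatement of the week-8 effect, only if the group main effect over baseline, week 4 and week 8 is reported, and a per-outcome error rate of 7-8% to 12%, depending on which tests are read.
- **Not supported:** that the planned analysis is diluted as it stands, or that the FSS primary result is affected. The primary FSS test is the 8-week change and is excluded from the repeated-measures paragraph.

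The power figures rest on assumed correlations, an assumed 0.6 SD effect and equal correlation between visits. The document gives no planning values for VAS or grip.

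**What to change.** In section 2.11.2, for VAS, grip strength and by-visit FSS:

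1. Delete the RM-ANOVA option and specify one linear mixed model with weeks 4 and 8 as responses, the outcome's baseline as covariate, and treatment, visit and treatment-by-visit as fixed effects.
2. Name the week-8 treatment contrast, with its 95% confidence interval, as the between-group result.
3. State that the change-score test for VAS and grip is supportive.
4. State the visits at which VAS and grip are measured, so that the three measurements are unambiguous.

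The cost is a few lines of text and one model call per outcome, settled before unblinding. If the three-visit reading is right, it needs no new data. The primary test does not change. Under the assumptions above with ρ = 0.5, week-8 power for these outcomes rises from about 70% with the change test to about 82%.

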#### 2.11.3 Statistical methods for analyzing safety outcomes

All adverse events occurring during the clinical trial period will be summarized as frequencies and percentages by groups. The pattern of adverse events between groups will be analyzed using chi-square test or Fisher’s exact test.

For laboratory test results and vital signs, descriptive statistics will be presented by groups, and between-group comparisons will be conducted. For between-group comparisons, changes from baseline (post-8-weeks consumption minus pre-consumption) will be analyzed using independent *t*-test.

### 2.12 Data monitoring and auditing

Monitoring will be conducted to ensure the protection of participants’ rights and welfare, to verify that reported trial-related data are accurate, complete, and verifiable when compared with source documents, and to confirm that the trial is being conducted in compliance with the approved protocol, ICH and GCP/KGCP guidelines, case report forms, source documents, and applicable regulations.

The monitor will conduct regular site visits and maintain telephone contact with the site. During visits, the monitor will primarily review original participant records, investigational product accountability logs, and research files. Additionally, the monitor will carefully observe the progress of the trial and discuss any issues with the investigator if problems arise.

## 3 Discussion

This clinical trial was designed to evaluate whether the anti-fatigue effects of PKL extract observed in previous animal experiments also occur in humans. The trial was planned in accordance with the Korean MFDS’s functional evaluation guidelines for health functional foods related to fatigue improvement (27), representing a critical step in verifying the potential of PKL extract as a functional food ingredient through human clinical trials.

The anti-fatigue effects of PKL extract are expected to work through several metabolic pathways that will be assessed using consistent biomarkers across both the previous animal experiments and this clinical trial. In mice, PKL extract showed improvements in anaerobic metabolism (reduced blood lactate and LDH activity), protection against muscle damage (reduced CK levels), and enhanced exercise endurance (increased time to exhaustion in swimming and rotarod tests) (9). This clinical trial will measure these identical objective biomarkers in humans to verify whether similar physiological responses occur, while additionally exploring subjective fatigue assessments.

If PKL extract shows significant improvements in both subjective fatigue measures and objective exercise performance parameters consistent with the animal model findings, it will provide evidence for its development as a functional health food ingredient for fatigue improvement. Furthermore, this study aims to generate the necessary data to support the regulatory approval process for PKL extract as a health functional food, bringing this natural product one step closer to benefiting public health.

There are several limitations in this protocol. First, subjective assessment tools such as the Fatigue Severity Scale and Visual Analogue Scale have inherent limitations, though this is mitigated by objective exercise performance measurements and comprehensive fatigue-related biomarkers. Second, the 8-weeks intervention period may be relatively short considering the chronic nature of fatigue (28), and the absence of follow-up limits assessment of sustained effects. Third, our strict inclusion and exclusion criteria, while creating a homogeneous study population, may limit generalizability to broader populations with fatigue, including those with different BMI ranges or chronic conditions. Fourth, as a single-center study, there may be limitations in terms of selection bias and generalizability compared to multi-center trials.

## 4 Ethics and dissemination

### 4.1 Research ethics approval

The protocol of this clinical trial was approved by the Institutional Review Board of Wonkwang University Oriental Medical Hospital, Jeonju (approval number: WUJKMH-IRB-2024-0009).

### 4.2 Protocol amendments

The current version of the protocol is V1.1. If changes to the protocol become necessary, modifications will be made after discussion between the investigators and the sponsor, and will be implemented after obtaining IRB approval.

### 4.3 Consent

Participant consent will be obtained before enrollment in the study. The principal investigator or delegated investigators will explain the content of the clinical trial, expected effects, and safety profile of the investigational product to potential participants according to the attached explanatory document and consent form. Written informed consent will be obtained from those who voluntarily agree to participate in this research. Participants will be given sufficient time to make their decision after receiving the explanation.

### 4.4 Confidentiality

The records identifying the participants will be kept confidential, and the participants’ identities will remain confidential even when the results of the trial are published. All trial-related documents will record and distinguish participants by their identification codes rather than by their names.

### 4.5 Dissemination policy

This clinical trial aims to develop PKL extract as a functional health food ingredient for fatigue improvement. The results of this clinical trial will be submitted to the Ministry of Food and Drug Safety (MFDS) in Korea and published in a peer-reviewed journal.
